#### 5.5 Analysis for adherence

Compliance is assessed based on 1) the number of facilities that have adhered to the study protocol throughout the study period 2) the 24hr urinary sodium and potassium excretion; 3) site monitoring data on the 3-monthly checking on the salt supply, in against to the goal of consumption set by the interventionist according to the study plan;

Descriptive statistics on the percent of compliant facility (N (%)) will be summarized.

For urinary electrolytes, both descriptive and model analyses will follow the same approaches as that for the efficacy analyses according to variable's math character, categorical or continuous.

For salt supply monitoring data, descriptive statistics on the percent compliance (N (%)) will be summarized in total and by each region.

#### 5.6 Subgroup analysis

The following pre-specified subgroup analyses will be performed on the primary outcomes and safety outcomes stratified by:

- 1) baseline blood pressure:
  - a. normal: baseline SBP < 140mmHg and DBP < 90mmHg
  - b. stage 1: baseline BP 140-159/90-99mmHg
  - c. stage 2 or above: baseline SBP > 160mmHg or DBP > 100mmHg
- 2) hypertension status:
  - a. normotensive: baseline BP < 140/90mmHg and not taking antihypertensive medication within 2 weeks before baseline
  - b. hypertensive: had baseline SBP  $\geq$  140mm Hg or DBP  $\geq$  90mmHg, or on antihypertensive medications within 2 weeks before baseline
- 3) region:
  - a. Changzhi
  - b. Xi'an
  - c. Hohhot
  - d. Yangcheng
- 4) Sex:
  - a. Male
  - b. Female
- 5) Age
  - a. < 70 years
  - b.  $\geq$  70 years

Using 70 years as the cut-off is because the mean age at the baseline was about 71 years.
- 6) educational attainment
  - a. illiterate, semi-illiterate or completed primary school
  - b. completed junior high school or above

Results will be presented on forest plots in **Figure 3** with the interaction results alongside

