## 2.2 Secondary Purpose

- To investigate if salt substitutes would increase the prevalence rate of adverse reactions such as hyperkalemia, as well as whether the kidney function would affect that effect amongst the elderly in Nursing Homes by comparing the results against a control group.
- To investigate if the salt reduction strategies would decrease the development of cardiovascular diseases and the resulting deaths by comparing the results against a control group.
- To evaluate the degree of compliance and cost-effectiveness of adopting salt substitutes and the stepwise salt supply control in the elderly in Nursing Homes .
- To explore the efficacy of the intervention strategies on proteinuria in the elderly with damaged kidney function and whether the kidney function influences that effect.
- To evaluate the effect of the intervention strategies on fundus atherosclerosis.

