**Subgroup Analysis:**

Subgroup analysis will be conducted according to the baseline renal function (eGFR) stages to understand the effect modification of baseline renal function.

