**Figure 3. Forest plot for subgroup analysis**

Results from subgroup analysis by age, sex, region, educational attainment, baseline BP, baseline hypertensive status and baseline antihypertensive medication use will be summarized by forest plot.

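### The SAP omits the protocol's only planned subgroup analysis, by baseline eGFR, without declaring it; separately, its blood-pressure strata are neither exhaustive nor mutually exclusive

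*Supplement*

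**What the plan says.** **Protocol V1.4.** Section 9 names a single subgroup factor: "Subgroup analysis will be conducted according to the baseline renal function (eGFR) stages to understand the effect modification of baseline renal function". It serves the first bullet of section 2.2, which asks whether salt substitutes raise the rate of adverse reactions such as hyperkalaemia, and then "whether the kidney function would affect that effect amongst the elderly in Nursing Homes by comparing the results against a control group".

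**SAP.** Section 5.6 begins "The following pre-specified subgroup analyses will be performed on the primary outcomes and safety outcomes stratified by" and lists baseline blood pressure, hypertension status, region, sex, age and education. Its top blood-pressure stratum reads "stage 2 or above: baseline SBP > 160mmHg or DBP > 100mmHg"; stage 1 is written as 140-159/90-99 with no connecting word. On age it says "Using 70 years as the cut-off is because the mean age at the baseline was about 71 years".

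The lead-in to Figure 3 adds a factor that 5.6 does not list: "baseline BP, baseline hypertensive status and baseline antihypertensive medication use will be summarized by forest plot". The figure's panels show this as potassium-sparing drug use, yes or no, and they split age at 65.

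Section 5.9, the table of changes from the protocol, covers the primary outcome and its model, the continuous secondary outcomes and an added renal-dysfunction outcome. It says nothing about subgroups.

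**The concern.** The protocol's background says that earlier reassurance on potassium chloride concerned people with normal kidney function, and that evidence in the elderly is thin. Its safety section makes low eGFR a criterion for the high-risk monitoring group. Yet the SAP, followed as written, examines safety by region, sex and education but not by kidney function, and gives no reason.

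The blood-pressure strata are a separate matter. Strata that leave some residents out, or place some in two groups, give a subgroup result that depends on how the programmer reads an unclear definition.

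**Working it through.** **1. Where baseline eGFR appears**

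| Place | Role of eGFR |
|---|---|
| Protocol 9, subgroup analysis | Effect modifier; the only subgroup named |
| SAP 1.2, safety aim | Not mentioned; hyperkalaemia risk overall |
| SAP 2.3, renal dysfunction | Outcome (new eGFR <60) |
| SAP 5.3.2.1, secondary hyperkalaemia analysis | One of several conditions adjusted for (eGFR <60) |
| SAP 5.6 and Figure 3 | Absent |
| SAP 5.9 | Removal not recorded |

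An adjusted model without a product term returns one intervention effect common to all eGFR levels. It cannot show whether that effect differs by kidney function. Using eGFR as an outcome does not show it either. No SAP analysis therefore covers the modifier clause.

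The first clause, whether salt substitute raises hyperkalaemia, is covered by the definition in SAP 2.3, the mixed logistic model in 5.3.2.1, the monitoring data in 5.3.3, and Tables 6 and 7.

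**2. Blood-pressure strata**

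Inputs from SAP 5.6: normal is SBP <140 and DBP <90; stage 1 is 140-159/90-99; stage 2 is SBP >160 or DBP >100. Stage 1 was read both ways.

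| Reading | Stage 1 = *and* | Stage 1 = *or* |
|---|---|---|
| 160/80, 130/100, 160/100 | none | none |
| 150/80, 130/95, 160/95, 150/100 | none | stage 1 |
| 150/105, 165/95 | stage 2 | stage 1 and stage 2 |

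All whole-number pairs with SBP 90-220, DBP 40-130 and DBP below SBP were then enumerated. Under *and*, 1,565 pairs fit no stratum and none fits two. Under *or*, 90 fit none and 1,200 fit two. These are grid points, not people. The next item in 5.6, hypertension status, uses >=140 or >=90, so its pressure limits do meet.

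**3. How many residents**

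The documents give an SBP standard deviation of 18 (protocol section 10) but no mean and no DBP distribution. What follows is illustration on assumed values.

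Readings of exactly 160, normal SBP with mean m: P = (1/18) × φ((160 − m)/18), multiplied by 960.
- m = 130: 0.0055, about 5 people
- m = 138: 0.0105, about 10
- m = 145: 0.0157, about 15

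This count ignores DBP. It includes some people who are classified through a high DBP and leaves out readings with DBP exactly 100. If all readings were rounded to tens, m = 138 would give P(155-165) = 0.106, or about 100 people.

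For both pressures together, a simulation assumed a bivariate normal with DBP mean 75-85, DBP SD 10-12 and correlation 0.4-0.6:

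| SBP mean | *and*: in no stratum | *or*: in no stratum | *or*: in two strata |
|---|---|---|---|
| 138 | about 28-35% | 0.6-1% | 2-8% |
| 130-145 | about 23-41% | 0.4-1.4% | 1-11% |

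The missing connective matters far more than the boundary at 160.

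**4. Age and drug subgroup**

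Residents aged 65-69 are in the younger group under 5.6 and in the older group in both panels of Figure 3. Potassium-sparing drug use has rows in both panels but no entry in 5.6.

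**The case against.** Several points on the other side are fair.

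- **The whole purpose is not lost.** A reader might infer that the protocol's hyperkalaemia question goes unanalysed. It does not; only the kidney-function clause does.
- **Abandonment is not shown.** The SAP nowhere withdraws protocol section 9, and 5.9 does not list this as a departure. The documents support an unexplained omission, not a decision to drop the analysis.
- **The restored test may be weak.** No hyperkalaemia rate or eGFR distribution is given, so its power cannot be computed. This stands as a caution in interpretation. It is a reason to look at continuous serum potassium as well, not a reason for silence.
- **The age conflict is editorial.** A reader might infer that the cut could be picked after seeing results. Section 5.6 states 70 and ties it to the baseline mean age, which does not depend on outcomes; the 65 sits in an empty figure shell.
- **The drug subgroup is pre-specified**, through Figure 3. Only the list in 5.6 needs completing.
- **The faults are separate.** The blood-pressure and age cut-points have no bearing on the eGFR gap.

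An analyst might also put overlapping readings in the higher stage by convention. The SAP does not say so, and that would still leave 160/80 unplaced.

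**Conclusion.** The point holds within these limits. The protocol's one planned subgroup analysis, by baseline eGFR, is missing from SAP 5.6 and Figure 3 and undeclared in 5.9. The effect-modification clause of the first secondary purpose therefore has no SAP analysis. This rests on the text alone.

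The blood-pressure strata are defective on either reading of stage 1; this follows from the definitions and needs no assumption. The number of residents affected cannot be fixed from the documents. A single count, such as 10 of 960, should not be quoted as the size of the problem: it depends on an assumed mean and misses the larger ambiguity in stage 1.

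The age cut and the drug subgroup are minor corrections. The primary SBP analysis in the full analysis set is unaffected, so this should be corrected but does not threaten the main result.

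**What to change.** 1. Add baseline eGFR to SAP 5.6 with categories fixed now: <60 v >=60 mL/min/1.73m2, the cut the SAP already uses, supported by eGFR as a continuous variable. The protocol refers to eGFR stages but sets out no full scheme (only stage 4 appears, in safety monitoring), so the SAP must state its own categories.
2. Specify an intervention-by-eGFR interaction for SBP, serum potassium and hyperkalaemia, and note that the hyperkalaemia interaction may be imprecise.
3. Define stage 2 as SBP >=160 or DBP >=100, and stage 1 as neither normal nor stage 2. In the enumeration above, every pair then falls in exactly one stratum.
4. Use the 5.6 age cut of 70 in both panels of Figure 3, and list potassium-sparing drug use in 5.6.
5. Record the subgroup changes from the protocol in 5.9. If leaving out eGFR was intended, say so there and give the reason.

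The cost is SAP wording, some extra interaction models, and a separate display for hyperkalaemia, because Figure 3 is laid out for means and SDs. No new data are needed: creatinine, blood pressure, age and antihypertensive drugs are recorded at baseline, and eGFR is already in the SAP's baseline table.

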## 5.7 Sensitivity analysis

Sensitivity analysis will be performed as below:

- 1) the per-protocol analysis of outcomes
- 2) to assess the effect of intervention on SBP change from baseline to 24-month, we will first use multiple imputation to impute missing value at 24-month. Then we will perform mixed model to account for clustering. The model would be:

$$y_{ij} = \beta_0 + \mu_j + \beta_1 x_{ij} + \beta_2 c_{ij} + \sum BZ_{ij} + e_{ij}$$

$$e_{ij} \sim N(0, \sigma_e^2)$$

$$\mu_j \sim N(0, \sigma_{\mu_j}^2)$$

Where  $i$  represents the  $i^{\text{th}}$  subjects,  $j$  represents the  $j^{\text{th}}$  cluster (aka. facility),  $y_{ij}$  is the SBP difference measured for subject  $i$  in cluster  $j$ ;  $\beta_0$  is the mean outcome in the control group at baseline;  $\mu_j$  is a cluster random effect to allow for between-cluster heterogeneity;  $x_{ij}$  is an indicator of the intervention for subject  $i$  in cluster  $j$  (1 indicates receive intervention while indicates not receive intervention),  $\beta_1$  is the effect coefficient of intervention;  $c_{ij}$  is the baseline SBP measured for subject  $i$  in cluster  $j$ ;  $Z_{ij}$  is the covariates other than baseline SBP;  $e_{ij}$  is the random error for the measurement of subject  $i$  in cluster  $j$ .

- 3) Since it may take several months for SSSC to take effect, we will conduct a sensitivity analysis for SSSC after excluding data in 6-month.
- 4) Since more missing data was observed in Xi'an, we will perform a sensitivity analysis after excluding participants from Xi'an.
- 5) For the analysis of urine electrolytes, a sensitivity analysis will be conducted after excluding possibly incomplete 24h urine collection. Incomplete 24h urine sample is defined as urine volume < 500ml/d.
- 6) For the analysis of events, a sensitivity analysis will be conducted on all randomized participants, regardless of the availability of the baseline BP measurements.

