**Investigations on the elderly include:**

-Contents:

**Questionnaire: General Demographic Data:** Gender, age, ethnic group, education level, marital status, and medical insurance of the participant.

**Lifestyle Information:** Smoking, alcohol consumption, level of physical exercise, frequency of fruit and vegetable consumption.

**Level of Satisfaction in Meals:** How much they liked the meals provided by the nursing home, self-assessment of the level of saltiness in meals.

**Disease History:** Whether or not they are suffering from hypertension, diabetes, stroke, coronary heart disease, kidney disease, cancer, or COPD. As well as other disease histories and whether they are receiving treatment.

**Information on Antihypertensive Drugs:** Type, specification, and frequency of consumption of antihypertensive drugs.

**Occurrence of an Endpoint Event:** Whether or not there is all-cause mortality or cardiovascular events (coronary heart disease, congestive heart failure, heart arrhythmia, and stroke).

**Health Status:** Will be evaluated using the EuroQol Five Dimensions Questionnaire (EQ-5D).

**Physical Examination:** Weight, height, blood pressure, heart rate.

**Laboratory Examination:** Serum electrolytes (blood potassium), blood sugar and four items of blood lipid, kidney function (serum creatinine), and blood routine. Levels of 24-hr urinary sodium, urinary potassium, urinary creatinine, and quantitative microalbuminuria.

**Eye Fundus Examination:** Vision test and funduscopy.

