## 5.5 Follow-up

- Follow-up timings: 6, 12, 18, and 24 months after the randomization

Follow-up content: See the Table below.

- Follow-up method:

Questionnaire: Professional investigators who have undergone standardized training will read through and check the travel records and medication information of the nursing homes, as well as question the participants. The information will be further verified through the New Rural Co-operative Medical System.

Physical examination: A physical examination will be conducted on participants. Laboratory Examination: Participants will be required to empty their bladder and record the time in the morning. They will then be given a 24-hr urine bucket and urine cup to collect their urine over the next 24 hours. The urine collection will be stopped at the same time on the morning of the second day. The urine volume of the participants over 24 hours, left out situations of urine, and the start and end time of the collection will be recorded. After mixing the 24-hr urine sample thoroughly, 5ml of urine will be collected using a catheter and stored at -20°C. 4ml of venous blood will be collected from participants on an empty stomach on the morning of their physical examinations.

Research Follow-up Form

| 
Time
 
Items
                 | Preparation Period | Baseline | Follow-up Period |          |          |          |             |                                  | Early Withdrawal |
|--------------------------------------------------|--------------------|----------|------------------|----------|----------|----------|-------------|----------------------------------|------------------|
|                                                  |                    |          | Month 6          | Month 12 | Month 18 | Month 24 | At any time | Transferring to Another Hospital |                  |
| Signing of Informed Consent Form                 | √                  |          |                  |          |          |          |             |                                  |                  |
| Confirmation of Inclusion and Exclusion Criteria | √                  |          |                  |          |          |          |             |                                  |                  |
| Basic Information Page                           | √                  |          |                  |          |          |          |             |                                  |                  |

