## **2.3 Outcome definitions**

The primary outcome for the study is SBP assessed as continuous variable (in mmHg) evaluated during 24-month follow-up.

Secondary outcomes:

- 1) DBP assessed as continuous variable (in mmHg) evaluated during 24-month follow-up.
- 2) 24-hour urinary sodium (in mmol/d), potassium (in mmol/d), and microalbumin excretion (In mg/d) assessed as continuous variable evaluated during 24-month follow-up.
- 3) Incidence of hyperkalemia. A new case of hyperkalemia is defined as having serum potassium  $>5.5$  mmol/L at either month 12 or 24 among participants with normal serum potassium at the baseline, regardless of clinical manifestations.
- 4) the risk of developing all-cause mortality, cardiovascular events (fatal and nonfatal stroke, fatal and nonfatal myocardial infarction, hospitalization or death caused by congestive heart failure)
- 5) ED-5Q during 24-month follow-up.

- 6) Incidence of renal dysfunction: A new case of renal dysfunction is defined as having eGFR <60 at either 12 or 24 months with normal eGFR at the baseline, regardless of clinical manifestations.
- 7) Incidence of hyponatremia: A new case of hyponatremia is defined as having serum sodium <135 mmol/L at either 12 or 24 months with normal serum sodium at the baseline, regardless of clinical manifestations.
- 8) A cost-effectiveness measure will be estimated based on the incremental cost of achieving each 1-mm Hg reduction in SBP

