**Labs**

Total cholesterol, mean(SD)

LDL-C, mean(SD)

Triglycerides, median(IQR)

HDL-C, mean(SD)

Fasting glucose, mean(SD)

Serum potassium, mean(SD)

Serum sodium, mean(SD)

eGFR, mean(SD)

Urinary potassium, mean(SD)

Urinary sodium, mean(SD)

Urinary creatinine, mean(SD)

Urine volume, median(IQR)

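### The sensitivity analysis for incomplete 24-hour urine screens on volume alone and ignores the recorded missed voids and collection times, so it is a weak check on urinary sodium and potassium

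*Supplement*

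**What the plan says.** SAP 2.3 makes the urine measures secondary outcomes, expressed as daily totals: "24-hour urinary sodium (in mmol/d), potassium (in mmol/d), and microalbumin excretion (In mg/d) assessed as continuous variable". SAP 5.5 also lists "the 24hr urinary sodium and potassium excretion" among the measures of compliance.

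The main models for continuous secondary outcomes (SAP 5.2.1) apply no completeness criterion. Completeness appears once, in SAP 5.7 item 5, which covers urine electrolytes: "a sensitivity analysis will be conducted after excluding possibly incomplete 24h urine collection". The definition follows at once: "Incomplete 24h urine sample is defined as urine volume < 500ml/d".

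Protocol V1.4 collects more than volume. Its laboratory method, given in 5.2 for baseline and repeated in 5.5 for follow-up, states that "left out situations of urine, and the start and end time of the collection will be recorded". The baseline laboratory panel in 5.2 names "Levels of 24-hr urinary sodium, urinary potassium, urinary creatinine, and quantitative microalbuminuria". In the SAP, urinary creatinine appears only as a descriptive line in the baseline table shell.

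**The concern.** A daily total is right only if the whole day's urine is in the bucket. Lost urine lowers measured sodium and potassium in proportion to the loss. A volume cut-off detects low volume, which is not the same as missed urine: a resident with a high output can lose a large share and stay above the line, and a resident with a low output can lose nothing and fall below it.

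The trial plans to record the direct evidence (whether urine was missed, and how long the collection ran), yet the rule would keep a collection whose own record says that urine was lost. If few under-collections are removed, the sensitivity result will sit close to the main result whether or not under-collection matters, and a reader may take that agreement for robustness.

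**Working it through.** The plan derives no figure here, since 500 ml is a chosen cut-off. The check is what the cut-off does.

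**Step 1: from the rule alone, with no distribution assumed.** A collection that loses a share f of true volume V measures (1-f)V. It is flagged only if (1-f)V < 500, that is, V < 500/(1-f).

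| Share lost | Flagged only if true volume is below |
|---|---|
| 20% | 500/0.8 = 625 ml |
| 30% | 500/0.7 = 714 ml |
| 40% | 500/0.6 = 833 ml |
| 50% | 500/0.5 = 1000 ml |
| 60% | 500/0.4 = 1250 ml |

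Three cases applied literally:
- True volume 1600 ml, half lost: 800 ml is measured, the sample is kept, and excretion is halved.
- 900 ml handed in with a missed void on the record: kept.
- True volume 450 ml with nothing missed: excluded.

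**Step 2: size, under stated assumptions.** The documents give no urine volumes (the table shell is empty), no frequency of under-collection and no share lost. Assumed: V lognormal with median m of 800 to 1800 ml and CV 0.4 or 0.5; 25% of residents under-collect; f uniform from 20% to 60%; f and true excretion independent of V.

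With s = sqrt(ln(1 + CV²)), which is 0.385 for CV 0.4 and 0.472 for CV 0.5, the chance that a loss f is flagged is

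P(f) = Φ([ln(500/(1-f)) - ln m]/s).

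Example: m = 1500, CV 0.4, f = 50% gives Φ((ln 1000 - ln 1500)/0.385) = Φ(-1.05) = 0.146, so about 85% of such collections pass.

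The share of under-collections flagged is P(f) averaged over f. The share of complete collections flagged is P(0). Before any exclusion the mean loss is 0.25 × 0.40 = 10%. After it, the mean loss is 0.25·E[f(1-P(f))] divided by the proportion of all collections that are kept.

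| Median, CV | Under-collections flagged | Complete ones flagged | Mean loss after exclusion (10% before) |
|---|---|---|---|
| 800, 0.4 | 55.3% | 11.1% | 5.05% |
| 800, 0.5 | 54.5% | 16.0% | 5.51% |
| 1000, 0.4 | 35.3% | 3.6% | 6.74% |
| 1000, 0.5 | 37.5% | 7.1% | 6.82% |
| 1200, 0.4 | 21.3% | 1.2% | 7.96% |
| 1200, 0.5 | 25.0% | 3.2% | 7.81% |
| 1500, 0.4 | 9.6% | 0.2% | 9.05% |
| 1500, 0.5 | 13.4% | 1.0% | 8.77% |
| 1800, 0.4 | 4.2% | 0.0% | 9.57% |
| 1800, 0.5 | 7.2% | 0.3% | 9.32% |

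The rule flags about 4% to 55% of under-collections and leaves between half (5.05/10) and nearly all (9.57/10) of the mean loss. The 25% and the 20 to 60% range were not varied.

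**The case against.** The strongest defence is about reach. Item 5 is one sensitivity analysis of secondary outcomes; the primary outcome is SBP, and no primary estimate, test or power figure depends on it. The SAP itself calls the excluded samples only possibly incomplete, so it claims no more than a simple, reproducible screen. Further handling may sit in the Data Validation Plan, the separate cleaning procedure mentioned in SAP 3.5, or annexes that are not shown. The limit on reach stands in full. The possibility of handling elsewhere lowers certainty, but item 5 states the analysis definition itself, and nothing shown adds to it.

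The defence also rightly blocks several stronger readings that a reader might infer:

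- *Most under-collections pass, and almost all of the bias stays.* The documents supply no volumes. Under the assumptions above, the first part fails at a median of 800 ml. The second is a fair description only from about 1500 ml upward.
- *The between-arm comparison is biased.* The documents give no reason for under-collection to differ by arm. Equal proportional loss shrinks a difference in mmol/d by about that proportion and creates no spurious effect. On the log scale, which SAP 5.2.1 allows for heavily right-skewed outcomes, it cancels.
- *Urinary excretion is the main adherence measure.* SAP 3.2 rests compliance mainly on the number of adhering facilities and lists urine as other supporting information.
- *Creatinine is available for the outcome sample.* It is named in the baseline panel only. The month-24 schedule lists the 24-hour urine without its assays, so creatinine there is implied at best.
- *Microalbumin is covered.* Item 5 is limited to electrolytes.

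**Conclusion.** The point holds as a weakness in one sensitivity analysis. Volume is the only completeness criterion in the SAP, and the missed-urine and timing records that the protocol requires at both baseline and follow-up go unused in it. That collections with a recorded missed void can pass while complete low-volume ones are removed follows from the rule itself.

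How often this happens rests on assumption. The range in the table runs from a screen that catches just over half of the under-collections to one that catches almost none. Across all of it, at least half of the mean under-collection survives, so agreement between this analysis and the main urinary sodium and potassium result is weak reassurance. Nothing here bears on SBP.

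**What to change.** In SAP 5.7 item 5, treat a collection as incomplete if any of these holds:

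1. measured volume below 500 ml;
2. a missed void on the collection record;
3. a recorded duration outside a window around 24 hours that is fixed before analysis;
4. only where urinary creatinine was measured at that visit, creatinine excretion outside a range fixed before analysis.

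Scale excretion to 24 hours from the recorded start and end times. This corrects for duration only, not for missed voids, so item 2 is still needed. Keep the volume-only version as a second line, and report by arm how many collections each criterion removes.

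Items 1 to 3 need SAP wording and a few derivation lines, with no new data. The window and the creatinine range have to be chosen and justified by the trial team, because the documents supply no values. The price is more post-randomisation exclusions and a wider interval in this sensitivity analysis; the main urine analysis is unchanged.
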